### Potential Adverse Effects and Safety Procedures

Potential adverse effects related to VR exposure will be monitored throughout the intervention. These may include cybersickness symptoms such as dizziness, nausea, eyestrain, headache, or disorientation; temporary dissociative-like discomfort or a reduced sense of presence after leaving the immersive environment; and excessive emotional activation during anxiety-provoking social tasks. Before the first VR session, participants will be informed of these possible reactions and reminded that they may pause or stop the session at any time without penalty.

During each VR session, participants will be monitored through real-time behavioral observation, voice responses, task progression, and physiological indicators. Therapists will remain available to enter the VR room or provide support if the participant requests assistance or if the monitoring data suggest substantial distress. Sessions will be paused or terminated if the participant requests to stop, reports significant discomfort, shows signs of cybersickness, becomes unable to continue the task, or if the therapist judges that continuation may not be clinically appropriate.

After each session, therapists will conduct a debriefing to review the participant’s subjective experience, emotional responses, and any adverse reactions. Any adverse events will be documented by the research team and reviewed during supervision. Participants requiring additional psychological support will be referred to appropriate school, community, or clinical services.

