## Methods

### Trial Design

The design is a 2-arm, statistician-blind, parallel-group RCT to test whether the VR intervention, compared with a waitlist control condition, leads to a reduction in social anxiety among youth. Assessments will be carried out at 0 (baseline, T0), 1 (posttreatment, T1), and 3 (follow-up, T2) months. A summary of the trial design can be seen in Figure 1.

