### Control Group: Waitlist Control

Participants in the waitlist control group will have access to the VR intervention withheld until after the 3-month follow-up assessment. To prevent confounding effects from relevant concomitant care and interventions, participants will be required to refrain from receiving any other treatments or interventions specifically targeting social phobia during the study period. The rationale for this comparator is that this study is an early-stage RCT designed to estimate the preliminary efficacy, acceptability, feasibility, and safety of a newly developed therapist-facilitated VR intervention in a youth population in Hong Kong. Before conducting a more complex and resource-intensive active-controlled trial, it is necessary to first examine whether the intervention can be delivered as planned, whether participants can tolerate and engage with immersive exposure, and whether the study procedures, assessment schedule, and outcome measures are feasible. The waitlist design will also provide initial estimates of recruitment feasibility, adherence, dropout, outcome variability, and potential treatment signals, which can inform the design and sample size calculation of future trials. Providing delayed access also helps address ethical concerns by allowing control participants to receive the intervention after the primary assessment period.

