### Outcomes

Basic demographic and clinical data, including age, gender, region, and socioeconomic status, will be collected. The primary outcome will be the SPIN, while the secondary outcome will be the Patient Health Questionnaire-9 (PHQ-9) for depressive symptoms. All outcomes will be self-assessed using the following online measurements at baseline, 1-month (postintervention), and 3-month follow-up (Figure 4).

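### Safety is named as something the trial estimates, but the adverse-event elicitation it describes is tied to VR sessions, so it reaches one arm and about one of three months

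*Protocol article*

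**What the plan says.** In the Protocol article, *Control Group: Waitlist Control* justifies the comparator by calling the study an early-stage RCT "designed to estimate the preliminary efficacy, acceptability, feasibility, and safety of a newly developed therapist-facilitated VR intervention". The same section says that waitlist participants "will have access to the VR intervention withheld until after the 3-month follow-up assessment".

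*Potential Adverse Effects and Safety Procedures* sets the scope of monitoring: "Potential adverse effects related to VR exposure will be monitored throughout the intervention". It then describes two occasions:

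- In the session: "During each VR session, participants will be monitored through real-time behavioral observation, voice responses, task progression, and physiological indicators".
- After the session: "After each session, therapists will conduct a debriefing to review" how the participant felt and whether there were adverse reactions.

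The section adds: "Any adverse events will be documented by the research team and reviewed during supervision". That sentence is not limited to an arm or a period.

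*Trial Design* gives the timetable: "Assessments will be carried out at 0 (baseline, T0), 1 (posttreatment, T1), and 3 (follow-up, T2) months". *Outcomes* names SPIN and PHQ-9 and says: "All outcomes will be self-assessed using the following online measurements at baseline, 1-month (postintervention), and 3-month follow-up". *Statistical Analysis* compares both scales between arms with mixed models of the mean score. *Recruitment* states that a participant who endorses suicidal ideation is flagged and a crisis procedure starts; this rule is not limited to an arm.

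**The concern.** The comparator section includes safety among the purposes of a randomized trial with a waitlist arm. The safety section then describes elicitation that the waitlist arm cannot undergo and that closes in the VR arm about two months before follow-up ends.

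Social anxiety and low mood vary over time without treatment. Distress found by asking only VR participants, and only while sessions run, cannot be divided into what the intervention caused and what would have happened anyway. Deterioration after the last session would not be sought as an adverse event. The SPIN and PHQ-9 data at T1 and T2 could show part of it, but a mean difference in favour of VR can coexist with a minority who got worse.

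**Working it through.** **1. Where events are actively sought.** From the sections cited above:

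| | Months 0 to 1 (T0 to T1) | Months 1 to 3 (T1 to T2) |
|---|---|---|
| VR arm | In sessions and debriefings | None described |
| Waitlist arm | None described | None described |

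With 45 per arm (*Recruitment*) and 3 months of follow-up, planned follow-up is 90 × 3 = 270 person-months. The described elicitation covers at most 45 × 1 = 45 of these, and 45/270 = 1/6. This ignores attrition and assumes that the sessions span the first month, since T1 is labelled posttreatment.

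**2. The plan's own figure.** *Recruitment* gives d = 0.75, two-sided alpha 0.05, power 90% and 15% attrition. By normal approximation, n = 2 × (1.960 + 1.282)² / 0.75² = 37.4, rounded up to 38 per arm. Then 38/0.85 = 44.7, rounded up to 45. The stated 45 per arm reproduces. It is used here only to give 45 randomized and 38 completing per arm.

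**3. What a clean VR-arm record would show.** With no events in n participants, the exact one-sided 95% upper bound is 1 − 0.05^(1/n):

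- n = 45: 6.4%
- n = 38: 7.6%

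This bound follows from the sample size alone. The procedure as described gives no waitlist rate to set beside it.

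**4. Limits for individual worsening.** The limit in SD units is 1.96 × √(2(1 − r)), with r the test-retest reliability in the two outcome-measure sections:

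- SPIN, r = 0.73: 1.96 × √0.54 = 1.44 SD
- PHQ-9, r = 0.86: 1.96 × √0.28 = 1.04 SD

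The article gives no SD for either scale, so these cannot be turned into points here. The SD to be used must be fixed in advance.

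**5. Precision of a by-arm comparison.** The documents give no worsening rate, so equal rates of 5%, 10% and 20% in both arms are assumed. The approximate 95% half-width of the risk difference is 1.96 × √(2p(1 − p)/n):

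| Assumed rate p | n = 45 per arm | n = 38 per arm |
|---|---|---|
| 5% | ±9.0 points | ±9.8 points |
| 10% | ±12.4 points | ±13.5 points |
| 20% | ±16.5 points | ±18.0 points |

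The comparison can therefore be descriptive only.

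**The case against.** The strongest reply has four parts.

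- **Recording is not confined to sessions.** A reader might infer that no adverse event can be recorded in the waitlist arm or after T1. The documents do not support that. The sentence on documenting adverse events has no limit by arm or time, and the suicidal-ideation rule applies to any participant. This part stands. What remains is narrower: those provisions do not describe asking anyone outside the VR sessions. The documentation sentence sits in the after-session paragraph and is tied to supervision, and the suicidal-ideation rule is a crisis response, not a reported outcome.
- **No comparative safety aim is stated.** A reader might infer that the trial fails such an aim. Safety as something to be estimated appears only in the comparator rationale, not in the objectives, hypotheses or conclusions. That rationale speaks of whether participants tolerate immersive exposure, which is a VR-arm question. This also stands, and it is why rewording the aim is an acceptable alternative. But the word safety is used to justify having a control arm, and the described procedure gives that arm no part in it.
- **The article condenses a fuller document.** An analysis plan may define deterioration tables, and the schedule figure is not shown. The lack of such a table is accordingly not the finding. The finding rests on the scope that the safety section states, set against the stated purpose.
- **Chance worsening would not inflate the VR record.** A reader might infer that random SPIN increases would be counted as harm on a VR-only list. The safety section lists reactions seen in or after sessions; SPIN change is not among them. Entry at SPIN 25 or higher also makes chance increases less likely through regression to the mean. No such inflation is claimed.

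**Conclusion.** The concern holds in limited form. Described elicitation of adverse events is tied to VR sessions and their debriefings. It reaches one of two arms and about 1 of 3 months, at most one sixth of planned person-time. Events sought in this way cannot be compared with the untreated course, and later deterioration would not be sought.

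This assumes that sessions end by T1 and that neither the unseen schedule figure nor a fuller protocol adds elicitation for both arms. If either does, the article only needs to say so. The primary efficacy analysis is unaffected, and how harms are managed clinically is not in question. This is a cheap improvement to how the trial addresses safety, not a flaw that undermines it.

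**What to change.** 1. **Use data already collected.** Report by arm, at T1 and at T2, the number and proportion with reliable SPIN worsening (for example, an increase above 1.44 SD), with PHQ-9 worsening (the same formula gives 1.04 SD) and with endorsement of the PHQ-9 self-harm item. Give risk differences with exact intervals, state in advance which SD is used, and label the table descriptive because of the widths above.
2. **Ask both arms the same question.** Add one short adverse-event item to the existing online forms at T1 and T2, worded identically for both arms.
3. **Keep VR-specific effects separate.** Cybersickness and similar reactions stay a description of the VR arm.
4. **If this is not done,** reword *Control Group: Waitlist Control* so that safety is an uncontrolled description of in-session VR tolerability.

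**Cost:** one table and one or two form items, with no change to the crisis or session procedures. Participants already past T1 will lack the new item at that visit. Those enrolled in March 2026 would have reached T2 in about June 2026, before the July 2026 date that the article gives for its exchange rate. *Results* has recruitment running through December 2026, so later participants can be covered. The change should start on the same date in both arms, and the item should be compared only among those randomized early enough to receive it at both visits. The answers will be unblinded self-report, which should be stated beside the table.

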### Pilot Study

A pilot study, conducted from January 2025 to April 2025, interviewed 26 individuals with SPIN scores of 25 or higher in Hong Kong to identify the most anxiety-provoking social situations and inform VR scenario design. Participants were asked: “What social settings do you fear the most, such as public speaking or interviews?” Based on their responses, the top 6 most anxiety-inducing situations were identified, including public speaking and job interviews. These findings will guide the development of VR scenarios that replicate realistic high-anxiety situations, ensuring the intervention effectively targets key challenges faced by individuals with social anxiety. Further details of the pilot study will be provided in a forthcoming article titled “Ecological Drivers of Youth Social Anxiety and Stakeholder Perspectives on Virtual Reality Intervention Design: A Qualitative Study in Hong Kong and Mainland China”.

To obtain a broader ecosystem perspective, interviews were conducted with 4 mental health professionals and 1 parent, eliciting views on adolescent social anxiety and their day-to-day challenges. The semistructured guide elicited participants’ views on adolescent social anxiety across five domains: (1) the current prevalence and presentation of the problem, (2) perceived etiological factors, (3) existing supports and resources, (4) gaps or areas in need of improvement, and (5) opinions on whether, and how, VR technology could assist youth with social anxiety.

According to the pilot results, the VR intervention was designed to address the unique characteristics of youth with social anxiety and incorporate suggestions from local mental health professionals. As a result, it stands out from existing VR interventions with 5 key innovative features:

Targeted focus on social phobia: unlike general VR exposure therapy, this VR intervention is specifically designed to address social anxiety, providing immersive scenarios tailored to gradually expose participants to anxiety-inducing social situations.Autonomous VR sessions: the system operates without requiring a therapist to be physically present. If no response is detected for 30 seconds, a prompt appears asking the participant whether they need a break or would like to invite a psychologist into the session for real-time support.AI-integrated feedback system: equipped with Doubao AI, the system provides real-time prompts and encouragement based on physiological and behavioral data. For instance, if an elevated heart rate is detected, the AI may prompt: “You’re doing great! Remember the deep breathing exercise from last time? Let’s try it together—inhale for 3 seconds...exhale.”Wearable device integration: participants wear a smartwatch that tracks EDA and HRV during VR sessions. These physiological responses are monitored in real time and displayed on the back-end CP, allowing therapists or researchers to assess stress levels remotely.Gamification and reward system: this VR intervention includes a point-based system where participants earn experience points for completing tasks. These points can be exchanged for rewards, such as customizing their avatar’s appearance in the virtual world, enhancing engagement and motivation.

### Control Group: Waitlist Control

Participants in the waitlist control group will have access to the VR intervention withheld until after the 3-month follow-up assessment. To prevent confounding effects from relevant concomitant care and interventions, participants will be required to refrain from receiving any other treatments or interventions specifically targeting social phobia during the study period. The rationale for this comparator is that this study is an early-stage RCT designed to estimate the preliminary efficacy, acceptability, feasibility, and safety of a newly developed therapist-facilitated VR intervention in a youth population in Hong Kong. Before conducting a more complex and resource-intensive active-controlled trial, it is necessary to first examine whether the intervention can be delivered as planned, whether participants can tolerate and engage with immersive exposure, and whether the study procedures, assessment schedule, and outcome measures are feasible. The waitlist design will also provide initial estimates of recruitment feasibility, adherence, dropout, outcome variability, and potential treatment signals, which can inform the design and sample size calculation of future trials. Providing delayed access also helps address ethical concerns by allowing control participants to receive the intervention after the primary assessment period.

### Outcomes

Basic demographic and clinical data, including age, gender, region, and socioeconomic status, will be collected. The primary outcome will be the SPIN, while the secondary outcome will be the Patient Health Questionnaire-9 (PHQ-9) for depressive symptoms. All outcomes will be self-assessed using the following online measurements at baseline, 1-month (postintervention), and 3-month follow-up (Figure 4).

**Figure 4. F4:**
[figure not shown]
SPIRIT (Standard Protocol Items: Recommendations for Interventional Trials) schedule throughout the study period. PHQ-9: Patient Health Questionnaire-9; SPIN: Social Phobia Inventory; VR: virtual reality.

#### Primary Outcomes: SPIN

Developed by Connor et al [22], SPIN is a brief self-report tool consisting of 17 items that assess fear, avoidance, and physiological discomfort in social situations. It is specifically designed for use with social anxiety disorder [23]. The Chinese version of the SPIN has been examined with good internal consistency (Cronbach *α*=0.85) and test-retest reliability (*r*=0.73). A cutoff value of 25 or higher has demonstrated strong reliability and validity and is commonly used to screen for social anxiety in the Chinese population [24].

#### Secondary Outcomes: PHQ-9

The PHQ-9 is widely used to screen for the presence and severity of depression, monitor the severity of depression over time, and assist with the diagnosis of depression. Each of the 9 items is scored from 0 (“not at all”) to 3 (“nearly every day”), with a total score ranging from 0 to 27. Higher scores indicate more severe depressive symptoms. PHQ-9 scores of 5, 10, 15, and 20 represent mild, moderate, moderately severe, and severe depression, respectively. The Chinese version of the PHQ-9 demonstrates high internal validity and consistency, as evidenced by a Cronbach α of 0.86 and strong test-retest reliability with a correlation coefficient of 0.86, affirming its efficacy for use in Chinese-speaking populations [25].

#### Adherence and Perceived Real-World Application

To assess participant adherence, a fidelity rating scale will be used, specifically measuring key aspects, such as session attendance and completion of assigned homework. Real-world application is a critical issue in evaluating intervention efficacy. To explore perceived real-world application, a mixed methods approach was used. A custom self-report questionnaire was administered at posttreatment and follow-up to measure perceived changes in social functioning, academic or occupational engagement, and real-life application of coping strategies. Items assessed outcomes, such as reduced avoidance, greater participation in daily tasks, and satisfaction with the intervention’s relevance to everyday life. To complement these data, semistructured interviews explored how participants applied therapeutic gains in real-world contexts, including specific examples of social interactions, academic challenges, and emotional regulation.

#### Physiological Data

HRV and EDA data collected during VR sessions will be analyzed using repeated-measures ANOVA to examine within-subject changes across sessions and between-group differences over time. For EDA, any fluctuation exceeding 2 SDs from the participant’s baseline, sustained within a 5-second window before and after the peak, will be flagged as an arousal event. These events will be quantified per session and used as indicators of physiological reactivity. Their frequency and timing will be explored in relation to session content and subjective distress and may serve as predictors or correlates of treatment engagement and emotional processing.

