### Recruitment

The trial will enroll 90 participants, allocating 45 to each arm. Allowing for 15% attrition, this sample provides 90% power to detect a treatment effect at T1, assuming an independent samples 2-tailed *t* test, an *α* level of .05, and Cohen *d* of 0.75. The target size also accords with comparable 2-arm VR intervention studies [16].

The first participant was enrolled in March 2026. The study will recruit participants from various settings in Hong Kong, including middle schools, tertiary institutions, and community centers. Adequate participant enrollment will be facilitated through partnerships with collaborating institutions, which will post digital flyers and promotional videos on their social-media platforms to reach the target population. The participants’ inclusion criteria were as follows: youth aged 15 to 25 years with a score of 25 or higher on the Social Phobia Inventory (SPIN). The exclusion criteria were as follows: (1) inability to attempt a baseline assessment (eg, due to being unpermitted to leave a psychiatric ward); (2) photosensitive epilepsy or significant visual, auditory, or balance impairment; (3) currently receiving another intensive psychological intervention; (4) a history of neurological conditions (eg, traumatic brain injury); and (5) insufficient language proficiency to understand the intervention requirements. In this trial, any endorsement of suicidal ideation will trigger crisis intervention procedures. Participants will be promptly flagged, and a trained clinician will notify the school or guardian to ensure appropriate safety measures are taken. School tutors or social workers familiar with students’ mental health will help identify participants unsuitable for the study, especially those whose conditions may be masked in self-report questionnaires. Participants will be recruited and screened online or offline, but will complete all interventions offline. Participants will be briefed through tutorial video clips demonstrating the research flow regarding intervention procedures, timing, and frequency.

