#### Intervention Design and VR Scenarios

The intervention comprises 6 sessions of 60 minutes each. This structure could be effective and practical for the target demographic in Hong Kong, considering the efficacy of brief interventions, challenges with longer program retention, and the need for adaptability to the local context [21]. There are 6 VR scenarios: a café, classroom, interview room, public bus, social gathering, and family gathering. Each scenario consists of 10 sequentially structured tasks, increasing in difficulty over time. For example, in a job interview scenario, task 1 involves the participant interacting with a friendly interviewer. Task 2 introduces a neutral, more serious interviewer. Task 3 features a foreign language–speaking interviewer, requiring the participant to respond in a nonnative language (eg, English). Before each task, participants will see an automated dashboard through the VR headset, providing background information and clear instructions on required actions, such as introducing themselves by saying, “Hello, my name is Chan Da Men.” To enhance engagement and support, the system monitors response time and, if no response is detected within 20 seconds, automatically displays assistance options, including taking a short break, requesting support from a psychologist, or extending response time. This structured approach ensures that participants receive gradual exposure, real-time guidance, and adaptive support, enhancing learning, confidence, and anxiety management in the VR intervention.

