#### Secondary Analyses

A similar linear mixed effects modeling approach will be used for secondary outcomes, including depressive symptoms measured by the PHQ-9. Exploratory analyses will examine adherence indicators, including the number of sessions attended, task completion, and homework completion. Where appropriate, adherence may be examined as a predictor or moderator of symptom change. Physiological indicators, including HRV and EDA, will be analyzed descriptively and, where data quality permits, using repeated-measures models to explore within-participant changes across sessions and associations with subjective outcomes.

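### The protocol names repeated-measures ANOVA for HRV and EDA over six VR sessions, which in its classical form uses only complete series, while its analysis section describes the same data more loosely; one all-available-data model should be named in both places

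*Protocol article*

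**What the plan says.** Two sections of the protocol article give an analysis for the same sensor data.

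- Outcomes, Physiological Data: "HRV and EDA data collected during VR sessions will be analyzed using repeated-measures ANOVA to examine within-subject changes across sessions". The same sentence also promises a comparison of the two arms, and it carries no condition.
- Statistical Analysis, Secondary Analyses: the two signals "will be analyzed descriptively and, where data quality permits, using repeated-measures models to explore within-participant changes across sessions".

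The surrounding facts are these.

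- Intervention Design and VR Scenarios: "The intervention comprises 6 sessions of 60 minutes each", so the repeated factor has six levels.
- Recruitment: "The trial will enroll 90 participants, allocating 45 to each arm".
- Potential Adverse Effects and Safety Procedures: "Sessions will be paused or terminated if the participant requests to stop, reports significant discomfort, shows signs of cybersickness".
- Secondary Analyses also treats the number of sessions attended as an adherence variable, so incomplete attendance is expected.
- Missing Data and Dropout-Related Bias relies on linear mixed models under missing at random for outcome data. It does not mention session-level sensor data.
- Control Group: Waitlist Control withholds the VR program until after the 3-month assessment.

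**The concern.** Classical repeated-measures ANOVA works on a complete participant-by-session table. One unusable session takes out the participant, including the sessions that were recorded well. The protocol itself points to three sources of gaps: stopped sessions, missed sessions and poor signal.

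The analysed set would then be the participants with six usable recordings. If those who react most strongly are more likely to stop, the arousal levels describe completers and not the VR arm, and precision is lost. The protocol already uses a model family that avoids this for SPIN and PHQ-9, so the choice of ANOVA here gains nothing. A reader also cannot tell which of the two descriptions governs.

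**Working it through.** **1. The plan's own figures.** The protocol gives no sample size, power or missing-data rate for HRV or EDA. Its only related figure is the 15% in Recruitment, which belongs to the T1 comparison. That calculation reproduces by the normal approximation: n per arm = 2(1.960 + 1.282)² / 0.75² = 37.4, so 38; 38 / 0.85 = 44.7, so 45 per arm and 90 in total. The 15% is an allowance for losing the T1 outcome in both arms, not a rate of incomplete session series.

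**2. Does the method need complete series?** In a check on 45 × 6 = 270 simulated values with one session deleted, a standard repeated-measures ANOVA routine (statsmodels AnovaRM) stopped because the data were unbalanced. A random-intercept mixed model on the same data kept all 45 participants and 269 sessions.

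**3. How many series would be complete?** Let q be the probability that a session is missing or unusable, independent between sessions (assumed; the protocol gives no value). Expected complete cases are 45 × (1 − q)⁶. If 15% dropout is assumed as well, they are 45 × 0.85 × (1 − q)⁶.

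| q (assumed) | (1 − q)⁶ | No dropout | 15% dropout also assumed |
|---|---|---|---|
| 0 | 1.000 | 45.0 | 38.3 |
| 3% | 0.833 | 37.5 | 31.9 |
| 5% | 0.735 | 33.1 | 28.1 |
| 10% | 0.531 | 23.9 | 20.3 |

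**4. What does that cost?** Simulation with 3,000 replicates, 45 participants, six sessions, within-person correlation 0.6, a true change of −0.5 SD from session 1 to session 6, and dropout that depends on arousal at the previous session, set to 15%. All of these inputs are assumptions. The table gives the standard error of the session 1-to-6 change, in SD units.

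| Added session loss | Complete cases | Mixed model, all usable sessions | Ratio |
|---|---|---|---|
| None | 0.146 | 0.143 | 1.02 |
| 5% | 0.172 | 0.146 | 1.18 |
| 10% | 0.203 | 0.152 | 1.34 |

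The complete-case estimate of the change is about −0.48 against the true −0.50. The completers' session-1 level is about 0.1 SD below the arm mean.

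**5. The between-group part of the sentence.** The data are those collected during VR sessions. The waitlist arm has none before the 3-month assessment, so there are no control values for a between-group comparison over the study period, whatever model is used.

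**The case against.** The strongest reply is that the loss is not certain. No section states listwise deletion. Secondary Analyses makes the modelling conditional on data quality, and its term, repeated-measures models, can include mixed models. Descriptive summaries can use every usable session. This stands: exclusion follows only if Physiological Data is read alone and ANOVA is taken in its classical form. What remains is that one section names an ill-suited method without condition and the other does not correct it.

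A reader might infer from "Allowing for 15% attrition" that the plan's own attrition removes 15% of the VR arm from this analysis. The documents do not support that. A participant can attend all six sessions and miss T1, or miss a session and complete T1. Even if the figure is borrowed, dropout alone costs only about 2% in standard error (0.146 against 0.143). The material loss comes from session-level gaps, whose rate is assumed. A shortened session may also still yield usable HRV and EDA, so not every terminated session is a missing one.

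A reader might also infer that the estimated change is seriously biased. Under the assumptions used it is not. The shift of about 0.1 SD is in the session-1 level, which is not the stated target.

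Finally, a condensed article may leave the handling of missing sessions to a fuller document. That is fair for detail left out, but here the article names a specific method.

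**Conclusion.** The point holds as a minor one. Physiological Data fixes a method that, in its classical form, cannot use incomplete six-session series, the protocol foresees such series, and Secondary Analyses describes the same data differently. The harm is lost precision and a completers-only set: with 15% dropout assumed, a standard error about 18% larger at 5% session loss and about 34% larger at 10%. These sizes rest on assumed loss rates, independence between sessions, a correlation of 0.6 and arousal-dependent dropout; the protocol gives none of these for the sensor data.

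No hypothesis, primary or secondary outcome, power figure or cost result is affected. Separately, and without any assumption about loss rates, the comparison between groups has no control data during the study period.

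**What to change.** - In Physiological Data, replace repeated-measures ANOVA with a linear mixed model that has session as a fixed factor and a participant random intercept, fitted to every usable session of every VR participant.
- Name the same model in Secondary Analyses, so that the two sections agree.
- Limit the model to the VR arm and delete the reference to between-group differences over time.
- Report the number of usable sessions per participant.

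The cost is a sentence or so in each of the two sections. No new data are needed, and the model family is already planned for SPIN and PHQ-9.
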